### 2.1. Interventions

Both the evaluations and the treatment will be conducted in the care unit of the University of Malaga and University of Castilla-La Mancha (Spain). To facilitate the adherence of the participants, a weekly follow-up will be performed by two physiotherapists ([name] and [name]) via phone call, through which the participants will be reminded of their appointments. The different interventions will be carried out by two physiotherapists ([name] and [name]).

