## 2. Materials and Methods

A protocol of a randomized clinical trial is presented with a blind randomization in the evaluation ([name]) and in the data analysis ([name]). The present protocol was registered in the platform https://register.clinicaltrials.gov/ (accessed on 16 November 2021) (NCT05122325). The study will be carried out according to guidelines and recommendations established for protocols by the SPIRIT statement [27].

The study is aimed at women with incomplete SCI, after which they had presented some type of SD. The candidates who participate in the study must meet the following inclusion criteria: women with American Spinal Injury Association or ASIA impairment B, C or D incomplete SCI (with preservation of the sacral arch and non-absent sensory evaluation of the lower dermatomes) below T6; aged 18–60 years without menopausal values of the follicle stimulating hormone (31–134 U/L) in a normal analysis; who present some type of SD secondary to SCI with at least 12 months of evolution; who live in Spain and are willing to go to the center of evaluations and treatments; and who sign the informed consent.

On the other hand, the study will exclude those women with active pregnancy and those who present pre-existing pathologies in the genital area, genital malformation, previous neurosurgery that affects the capacity of genital response, SD prior to the SCI, pressure ulcers, severe medical disease or any type of pathology in which the use of low frequency is contraindicated. In addition, the study will also exclude those with a psychiatric disorder or dependency on narcotics, and those who use selective serotonin reuptake inhibitors, antipsychotics or other drugs that affect the sexual response.

Regarding the sample size predicted for this study, 15 subjects were estimated for each group, with an effect size of 1.1, Df 28, α = 0.05, power (1 − β) = 0.80 (1 − β err prob) = 0.80u. Moreover, 20% more women will be recruited in order to consider the possible heterogeneity of the group and participants lost during the course of the study. Thus, a total of 54 women (18 women per group) will be recruited.

The project will be advertised in social networks, as well as in all the entities that belong to the ASPAYM (Association of people with spinal cord injury and other physical disabilities) in Spain.

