The participants will be selected by non-probabilistic sampling from among those women who will reply to the advert and those associated with ASPAYM, who will be called for an interview in the University of Malaga or in the University of Castilla-La Mancha. The women who meet the inclusion criteria described above and sign the informed consent will be randomized by the Spanish version of the OxMar software [28] to either the control group (*n* = 18), the TTNS group (*n* = 18) or the vibration group (*n* = 18). Such distribution will be known to the lead researcher ([name]), who will oversee and indicate to each participant, in a closed envelope, the group they will be assigned to (Figure 1).

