### 2.4. Data Analysis

Firstly, a test will be performed to determine the efficacy of the randomization of the baseline characteristics of the participants in the 3 groups through the Shapiro-Wilk test and normal distribution diagrams.

Secondly, we will establish the rate of adherence of the different participants randomized to each of the groups and their percentage of abandonment, comparing their effect through the *t*-test or Mann-Whitney *U*-test to determine whether the groups differ in the demographic variables in V0.

Thirdly, the comparisons to determine the effect of the interventions on FSFI, SQOL-F and the quantitative sensory tests in different time points will be analyzed with ANOVA, or Kruskal-Wallis for non-parametric samples, using the Bonferroni method for the multiple comparisons between different evaluation time points. The results will be considered statistically significant if *p* < 0.05. Moreover, the differences between each evaluation after the intervention and the arousal and orgasm before the intervention will be recorded in binary variables of “improvement of arousal/orgasm”, with values 0 (same or lower arousal) and 1 (greater arousal). Thus, improvement in all variables will be compared with the rate of participants who increase their sensation in the three groups through the risk ratio and the χ^2^ test. The data analysis will be carried out using the SPSS software v.25.0 (IBM, New York, United States).

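### Two study centres, but no balancing of allocation by centre is stated and the named tests carry no centre term: a modest loss of precision and an exposure to chance imbalance, not a bias

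*Protocol article*

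**What the plan says.** All references are to the protocol article.

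- **Entry (section 2, Materials and Methods).** Candidates are those "who will be called for an interview in the University of Malaga or in the University of Castilla-La Mancha". How a woman comes to one centre rather than the other, and the expected split, are not given.
- **Treatment and evaluation (section 2.1).** "Both the evaluations and the treatment will be conducted in the care unit of the University of Malaga and University of Castilla-La Mancha".
- **Staffing (section 2.1).** "The different interventions will be carried out by two physiotherapists". Nothing links either of them to a centre or to an arm.
- **Allocation (section 2).** Eligible women "will be randomized by the Spanish version of the OxMar software" to control, TTNS or vibration, with 18 in each. No stratification, blocking or minimisation factor is mentioned.
- **Sample size (section 2).** "15 subjects were estimated for each group, with an effect size of 1.1, Df 28, α = 0.05", with power 0.80. After a 20% increase, "Thus, a total of 54 women (18 women per group) will be recruited".
- **Analysis (section 2.4).** The effects on FSFI, SQOL-F and the sensory tests "will be analyzed with ANOVA, or Kruskal-Wallis for non-parametric samples". Improvement in arousal and orgasm is compared by risk ratio and a chi-square test. Centre does not appear in any of these.
- **Assessment (section 2.3).** One blinded researcher, trained beforehand, conducts the evaluations.

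**The concern.** Much of what happens at a session depends on where it happens and who runs it: placing electrodes, titrating intensity, training in the device, weekly visits and setting up the sham. The women seen at the two universities may also differ in case mix. If outcomes differ by centre, two things follow.

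- With arms of 18 and no balancing, the arms can by chance draw quite different shares of their women from each centre.
- Variation between centres that no model term removes stays in the error variance and lowers power.

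Both can be prevented cheaply, but the first only before enrolment. An analysis plan written later can add a centre term; it cannot balance an allocation already made.

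**Working it through.** **Step 1. Reproduce the planned sample size.** Inputs from section 2: d = 1.1, α = 0.05 (two-sided assumed, since sidedness is not stated), power 0.80. For a two-sample t-test with n per arm, df = 2n − 2 and the noncentrality is d√(n/2).

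- n = 14: power 0.79994, just short of 0.80.
- n = 15: power 0.828, with df = 2 × 15 − 2 = 28, as stated.
- 15 × 1.2 = 18 per arm, and 3 × 18 = 54.

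The planned figures reproduce and are not in dispute here. At 18 per arm the noncentrality is 1.1 × √9 = 3.3 and power is 0.894.

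**Step 2. Chance imbalance in centre.** The split is not given, so take 27 women from each centre (assumed): p = q = 0.5, N = 54, arms of n = 18, no balancing. For the difference D between two given arms in the number of women from one centre:

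- Var(D) = 2npq × N/(N − 1) = 2 × 18 × 0.25 × 54/53 = 9.17, so SD(D) = 3.03.
- Normal approximation with continuity correction: P(|D| ≥ 4) ≈ P(|Z| > 3.5/3.03 = 1.16) ≈ 0.25.

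Random permutations of 54 women into three arms of 18 (40,000 draws) give:

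| Centre split (assumed) | Two given arms differ by ≥ 4 | At least one pair of arms differs by ≥ 4 |
|---|---|---|
| 27/27 | 25% | 47% |
| 40/14 | 18% | 39% |

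With 27/27, gaps of 6 or more occur in about 7% of allocations for two given arms and in about 15% for at least one pair.

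**Step 3. Type I error.** In 200,000 simulated unbalanced allocations with 27 women per centre, an unadjusted t-test between two arms had an overall type I error of 4.9% with a centre difference of 0.5 SD and 5.0% with 0.8 SD. Ignoring centre does not inflate it.

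**Step 4. Precision.** Let the centres differ by δ within-centre SDs (assumed), half the women coming from each.

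- Unadjusted: the SD becomes √(1 + δ²/4), so the effective effect size is 1.1/√(1 + δ²/4). For δ = 0.5 this is 1.1/√1.0625 = 1.067; for δ = 1.0 it is 1.1/√1.25 = 0.984.
- Balanced, with a centre term: the effect size stays 1.1 and one degree of freedom is spent, so df = 2n − 3.

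| n per arm | Unadjusted, δ = 0.5 | Unadjusted, δ = 1.0 | Balanced with centre term |
|---|---|---|---|
| 18 | 0.875 | 0.818 | 0.893 |
| 15 | 0.805 | 0.739 | 0.827 |

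If there is no centre difference, the centre term costs almost nothing: 0.893 against 0.894 at 18 per arm, and 0.827 against 0.828 at 15.

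**The case against.** The strongest reply is that the article is silent rather than wrong. It names allocation software that may well have been set to balance on centre, and a journal article leaves much to the full protocol. Adjustment terms are commonly left to an analysis plan, which is not shown. This fixes the wording: no balancing by centre *is stated*, which is not the same as knowing that there is none. It does not dispose of the point. The article does describe the allocation, and it says that it follows SPIRIT, so a balancing factor would be expected there. Two of the tests it commits to, Kruskal-Wallis and the plain chi-square, cannot carry a centre term.

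A second reply is that centre differences in measurement are limited. One trained, blinded researcher does the evaluations, the women complete FSFI and SQOL-F themselves, and the sensory and arousal/orgasm results are also compared with each woman's own earlier state, so a stable difference in level largely cancels there. This stands, and the assumed 0.5 to 1.0 SD has no support in the documents. Differences between centres in delivery or in response to treatment would remain.

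Two stronger readings are tempting, and neither is supported:

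- *Ignoring centre raises the false-positive rate.* A reader might infer this by looking only at allocations with a large gap. Over all allocations the rate stays at 5% (step 3).
- *Physiotherapist is confounded with arm.* Section 2.1 would permit a split by intervention, but it does not state one. With two physiotherapists and two universities, one per centre is an equally open reading, and two people cannot match three arms one to one. A false-positive rate computed for complete overlap would describe a scenario that the document does not contain.

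**Conclusion.** The point holds as a matter of efficiency and chance imbalance. Centre appears in neither the stated allocation nor the stated tests of a two-centre trial with 18 women per arm. There is no bias and no inflation of the type I error.

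The loss of power at 18 per arm is about 0.02 if the centres differ by 0.5 SD (0.893 − 0.875 = 0.018) and about 0.075 if they differ by 1.0 SD (0.893 − 0.818). It would matter most if losses bring the arms down to 15. Unadjusted power is then 0.739 at a difference of 1.0 SD, below the planned 0.80, while at 0.5 SD it still meets the target at 0.805.

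These power figures rest on an equal centre split, an assumed centre difference, the planned effect of 1.1 expressed in within-centre SDs, and a two-sided comparison of two arms. The staffing question is a request for clarification, not a defect shown by the text.

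**What to change.** 1. **Allocation (section 2).** State centre as a balancing factor in the allocation software, with block sizes that vary within centre and are not disclosed to those who recruit. If the software has already been set up this way, say so.
2. **Analysis (section 2.4).** Add centre as a fixed factor in the models for FSFI, SQOL-F and the sensory tests. If the rank-based route is kept as the fallback, use a version stratified by centre.
3. **Staffing (section 2.1), secondary.** Add one sentence saying that the physiotherapists are not split by arm.

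The cost is one degree of freedom, allocations that are slightly easier to guess near the end of a block (which varying block sizes limit), and final arm sizes that may differ from 18 by one or two. The total of 54 need not change. Items 1 and 3 need to be settled before enrolment and treatment begin.

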#### 2.1.1. Intervention Group 1: Transcutaneous Tibial Nerve Stimulation

The women randomized to the TTNS intervention group will receive 12 stimulation sessions using a TENS^®^ EMS NMS60 device TENS, Madrid, Spain). These sessions will last 30 min each and will be conducted once per week at 10 Hz, with a pulse width of 200 μs and an intensity of 0–100 mA, which will be individually adjusted to each participant. Four electrodes will be placed: the first electrode 4–5 cm cephalad to the internal malleolus; the second electrode on the calcaneus area (Figure 2). Initially, the intensity will be gradually increased until the first toe shows flexion or abduction (motor threshold) or until the rest of the toes show flexion. Once the stimulation of the tibial nerve is ensured, the frequency will be raised to 10 Hz and the intensity will be lowered until the sensory threshold is reached [29].

#### 2.1.2. Intervention Group 2: Genital Vibration

The women randomized to the genital vibration intervention group will be trained in the use of the Ferticare 2.0^®^Medical Vibrator (Multicept, Rungsted, Denmark) accepted by the Food and Drug Administration), and each participant will be provided with one of these devices. Initially, a practical session will be carried out with them, explaining to them that the frequency of use will be 70 Hz, with an amplitude of 1.5 mm. It will be recommended to them to gradually increase its use in time, with a limit of 30 min per day. The intensity will be increased progressively until small vibrations are found [15]. The vibrating head can be placed in any of the 5 genital points innervated by the pudendal nerve (clitoris, bilateral labia majora and bilateral perineum), using the minimum pressure required to maintain the position [25]. They will be asked to use it once per week, before or during a sexual encounter, and they will also be required to record its use and any doubt related to it. Every week, a 30-min visit will be performed to check how they are using it and solve any doubts that may emerge.

#### 2.1.3. Control Group: Sham-Transcutaneous Tibial Nerve Stimulation

The guideline of application will be the same as that for the TTNS intervention group, but with the device switched off. The electrodes will be placed, and their location will be assessed to ensure that they are on the desired area. Once the intensity is lowered to reach the sensory threshold of the treatment, they will leave it at an intensity of 0. Then, the device in sham TTNS will be switch on for 30 s at the beginning, switch off for 20 min, and switch on for 30 s before stopping [30].

#### 2.1.4. Common Guidelines for the Three Groups

The interventions will be conducted throughout a period of 12 weeks. Prior to the interventions, the participants will be briefed on and given a handout with basic information and guidelines, common to all participants, focused on rediscovering sexuality after the SCI [31] (Table 1).

### 2.2. Outcome Measurement

The outcome will be the improvements obtained in FSFI, SQOL-F, sensory tests and specific improvement reported in orgasm and arousal.

The FSFI, whose use is supported by the Autonomous Standards Committee for the evaluation of sexual function in women with SCI [9], has been translated to and validated in Spanish [32], showing validity, internal consistency in all its domains (Cronbach’s Alpha of 0.745 in arousal and 0.753 in orgasm) and a test-retest reliability of ICC 0.96. This questionnaire consists of 19 questions, which are grouped into 6 domains. The score of each domain is multiplied by a factor and the final result is the arithmetic sum of the domains. The higher the score, the better the sexuality.

The changes in the quality of life will be objectified through the SQOL-F [33], which also showed good validity and reliability. The questionnaire was designed to measure the impact of SD on the quality of life [34]. This questionnaire consists of 18 questions with a response scale of 6 options. The sexual quality of life will be considered as follows: poor for a score of 18—51 points, moderate for 51–84 points, and good for over 84 points [35]. Additionally, the quantitative sensory tests will be used, whose validity has been proved in neurogenic female SD [36]. These tests consist in quantitatively measuring the sensory function in a non-invasive manner. Using a software-controlled probe, vibration is applied in a precise and controlled manner to the clitoral and vaginal areas, establishing the sensory thresholds of each participant, which are then compared with normal values established in previous studies to determine the presence of hyposensitivity or hypersensitivity and correcting the data for age.

Among these, previous studies have reported that vibratory stimuli are the most suitable to evaluate the sexual area [36]. Initially, the obtained results will be compared with the normal values obtained in previous studies [37], considering them as altered if they are outside of the confidence interval assigned to each age group, and, subsequently, with the previous values of each participant.

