The literature shows improvements in SD in women through the application of genital vibration [14,15] or transcutaneous tibial nerve stimulation (TTNS) [16,17]. With respect to transcutaneous peripheral neuromodulation through the tibial nerve (L4—S3) [18], this presents an area of easy access to such nerve, which shares the same metameric area with the somatic and parasympathetic innervation of the pelvic floor (S2—S4) [19]. It is believed that the stimulation of its sensory afferent fibers blocks the abnormal afferences of this nervous region [20]. Therefore, through this neuromodulation, it is possible to regulate or modify the nerve activity on the different structures [21] and balance the excitatory and inhibitory impulses that produce improvements in vaginal arousal and lubrication [16].

Regarding vibrators, the literature shows two uses: (1) applied in bursts, after which there is an increase in blood flow associated with arousal; and (2) continuous vibration, which stimulates the high sympathetic explosion related to orgasm [22], also resulting in a better tissue perfusion, which can help to reduce muscle tone and increase relaxation [23].

It is important to propose treatment options for SD in women after SCI, since, currently, only educational programs are provided in most cases at late stages, and the patients refer an important deficit of information and treatment of SD [24]. Furthermore, due to the heterogeneity of levels and complexity of SCIs, this study will analyze the effect of two possible interventions plus a control group. None of these two propositions of intervention have presented any adverse effect [25,26].

We hypothesize that both types of stimulation, combined with educational programs, improve the evaluated sexual dysfunction symptoms measured through the Female Sexual Function Index (FSFI) and the Sexual Quality of Life-Female (SQOL-F) questionnaire. Particularly, the application of low-frequency genital vibration improves orgasm and TTNS improves arousal in women with SCI. The aim of the present study is to evaluate the effectiveness on FSFI and SQOL-F of an educational program plus TTNS and vibration in women with SD after SCI.

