### 2.3. Data Collection

To preserve the confidentiality of the participants’ data, the researchers commit to complying with Organic Law 3/2018, of December 5th, on the protection of personal data and the Royal Decree that enforces it (RD 1720/2007). The participants will receive a code that will be related to the personal data only in a coding sheet. The evaluations will be conducted by a blinded researcher ([name]), who will initially collect the data of the participants in a data collection sheet: age, body mass index, data and type and level of spinal cord injury, pathologies or complications derived from the injury, allergies, pregnancies, type of deliveries and other diseases. Then, the participants trained by this researcher will complete the FSFI questionnaire, the SQOL-F, and the quantitative sensory test at the beginning of the treatment (V0, before the participants are randomized to any of the 3 groups), after the treatment (V1), and at 3 months (V2), 6 months (V3) and 12 months (V4) after the end of the treatment. [name] will be previously trained to standardize the measurements and will be blinded throughout the entire study to the randomization of the participants.

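### No primary outcome or visit is named and only time points are corrected, so a claim resting on any significant result has a false-positive chance well above 5%

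*Protocol article*

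**What the plan says.** - **Outcomes.** Section 2.2 gives five measures one shared status: "The outcome will be the improvements obtained in FSFI, SQOL-F, sensory tests and specific improvement reported in orgasm and arousal". No measure is called primary.
- **Aim.** The Introduction is narrower: "The aim of the present study is to evaluate the effectiveness on FSFI and SQOL-F of an educational program plus TTNS and vibration". The hypothesis there also links vibration to orgasm and TTNS to arousal.
- **Visits.** Section 2.3 sets four evaluations after baseline: "after the treatment (V1), and at 3 months (V2), 6 months (V3) and 12 months (V4) after the end of the treatment". None is marked as deciding.
- **Threshold.** Section 2.4: "The results will be considered statistically significant if *p* < 0.05".
- **Correction.** The only one stated is in the ANOVA/Kruskal-Wallis sentence of section 2.4, which covers FSFI, SQOL-F and the sensory tests: "using the Bonferroni method for the multiple comparisons between different evaluation time points".
- **Arousal and orgasm.** Section 2.4 turns each into a yes/no improvement at every post-treatment evaluation and compares it "in the three groups through the risk ratio and the χ^2^ test". No correction is attached.
- **Size.** Section 2: "Thus, a total of 54 women (18 women per group) will be recruited". The calculation behind it uses effect size 1.1, 28 degrees of freedom, α = 0.05 and power 0.80, and names no outcome.

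**The concern.** The article defines the outcome, a significance threshold and a multiplicity rule, so this is more than detail left to an analysis plan. The stated rule covers one source of multiplicity (visits) for three of the five measures. The number of outcomes, the two active groups each set against control, and the repeated χ² tests are not covered.

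At stake is the meaning of a positive result. The trial has two active groups, five measures and four post-treatment visits. Without a named outcome and visit, nothing written in advance says which result would show that TTNS or vibration works. A reader of the final report could not tell a pre-planned success from the best of many looks. A primary outcome chosen after the data are seen would not repair this.

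**Working it through.** **1. The plan's own figure.** A two-sample t-test with d = 1.1 and two-sided α = 0.05 has noncentrality d·√(n/2) on 2n − 2 degrees of freedom. Power is 0.7999 at n = 14 and 0.828 at n = 15, so 15 per group is the smallest size reaching 0.80, with 2·15 − 2 = 28 degrees of freedom. Then 15 × 1.2 = 18 and 3 × 18 = 54. The sample size reproduces, as one two-group comparison at 0.05 with no allowance for multiplicity.

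**2. Counting the tests.** Three continuous measures × 4 visits = 12 group tests; two binary measures × 4 visits = 8. Total 20, with one three-group test each. Five measures is a minimum: the sensory tests cover clitoral and vaginal areas, and FSFI has six domains.

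**3. Independent tests, no true effect.** The chance of at least one false positive is 1 − ∏(1 − αᵢ). Bonferroni over four visits gives 0.05/4 = 0.0125.
- Visit correction credited to all five measures: 1 − 0.95⁵ = 22.6%. The bound is 5 × 0.05 = 25%, whatever the correlations.
- Eight χ² tests alone at 0.05: 1 − 0.95⁸ = 33.7%.
- Twelve continuous tests at 0.0125 plus eight χ² tests at 0.05: 1 − 0.9875¹² × 0.95⁸ = 43.0%.
- FSFI and SQOL-F only, at one visit: 1 − 0.95² = 9.8%.

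**4. Correlated tests.** The article gives no correlations, so these are assumptions. Multivariate normal simulation under no effect, 100,000 runs per setting, one normal test statistic per group test:

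| Correlation: outcomes / visits | All five corrected over visits, one group test | χ² uncorrected, one group test | χ² uncorrected, two control contrasts |
|---|---|---|---|
| 0 / 0.3 | 21% | 41% | 62% |
| 0.3 / 0.5 | 19% | 36% | 56% |
| 0.3 / 0.7 | 16% | 30% | 49% |
| 0.5 / 0.5 | 17% | 32% | 51% |
| 0.5 / 0.7 | 14% | 28% | 45% |
| 0.7 / 0.8 | 10% | 21% | 35% |

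Patient-level simulations with 18 per arm, at correlations of 0.3–0.5 between outcomes and 0.5–0.7 between visits, gave:
- 10–13% for the three continuous measures alone;
- 30–41% with uncorrected three-group χ² tests added;
- 34–49% when the continuous measures are also compared as two active-versus-control contrasts.

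**5. Power after the fix.** With d = 1.1 and α = 0.025 (Holm's first step for two contrasts), power is 0.825 with 18 per group and 0.737 with 15. Correcting all 20 outcome-by-visit tests instead (0.05/20 = 0.0025) would leave 0.522 and 0.400.

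**The case against.** The strongest reply is that the plan does not fix any single error rate. A reader might infer a definite figure such as 36–51%, but the documents do not support one.

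- It needs assumed correlations and a rule that any one significant result counts as success. The article says only when a result is called significant.
- The upper part of that range also needs pairwise group tests on the continuous measures. Section 2.4 names ANOVA or Kruskal-Wallis there, and keeps the t-test and Mann-Whitney test for adherence, abandonment and baseline comparisons. It does not say whether the ANOVA is run at each visit or over time.
- If the visit correction is meant for all five measures, with one three-group test each, the rate cannot exceed 25%.

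A reader might also infer that all five measures are fully equal. That is true of section 2.2. The aim, however, puts FSFI and SQOL-F first, and section 2.2 introduces the sensory tests as an addition.

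Finally, the article is condensed, and an analysis plan or the registry entry may rank the outcomes. Neither is shown.

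These points limit the size but do not remove the defect. The informal ranking holds two co-equal measures and no visit, and it is not carried into sections 2.2 or 2.4. None of the readings examined brings the error down to 5%.

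**Conclusion.** The point holds in this form: no primary outcome or visit is named, and the stated correction does not hold the error of an effectiveness claim at 5%.

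The size is conditional on treating any significant result as success:
- about 10–25% on the generous reading, where visits are corrected for every measure and there is one three-group test each;
- roughly 30–50% with the χ² tests uncorrected as written, under moderate assumed correlations and with one or two group contrasts. The more extreme correlations in the table widen this to 21–62%.

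The conclusion that the error exceeds 5% does not depend on the choice among these readings; the exact figure does.

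**What to change.** **Section 2.2.** Before data are seen, name one primary outcome and visit, for example FSFI total score at V1. The aim gives FSFI and SQOL-F equal place, so the sponsor must choose. Make SQOL-F at V1 the first key secondary, so that the second half of the aim stays testable.

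**Section 2.4.**
- Test TTNS versus control and vibration versus control on the primary outcome with Holm at overall two-sided 0.05.
- Test the key secondaries in a written order: SQOL-F, then FSFI arousal for TTNS and FSFI orgasm for vibration. State the gatekeeping rule, for example that testing goes on only after both primary contrasts succeed, and fix the order of the two SQOL-F contrasts.
- Report the sensory tests, the binary improvements and V2–V4 as estimates with 95% confidence intervals.

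**Section 2, sample size.** Name the outcome that the calculation refers to, and restate power at the adjusted level (0.825 with 18 completers per group, 0.737 with 15).

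**Cost.** No extra participants are needed if all 18 per group complete. With 15 completers the power falls below the stated 0.80, and the Limitations paragraph itself warns of high abandonment. Some secondary results can no longer be called significant, and under the example gate one failed primary contrast closes the whole secondary sequence. The registry entry should be aligned with the revised text.
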